### Sample size and statistical analysis

Since this trial is a phase I pilot study, each group is composed of three subjects to examine the safety of HUNS001–01 administration. The sample size of the trial was based on the traditional 3 + 3 dose escalation design. The first three subjects are included in the low-dose group (cell dose: 2 × 10^7^ cells), and the following three patients are included in the high-dose group (cell dose: 5 × 10^7^ cells). However, if the cultured BMSCs are inadequate for the high-dose group on 74 days after the onset of stroke, a subject could be moved to the low-dose group, if possible. In that case, the number of subjects will exceed six, and the last subject is the third subject in the high-dose group. The total number of subjects is limited to 10 if a third subject in the high-dose group is not accomplished.

Continuous data will be presented as means and standard deviations. Categorical data will be presented as absolute frequencies or relative percentages.

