### Safety measures for intraparenchymal injection

Intraparenchymal injection is a technique to administer cells directly into the cerebral parenchyma. This technique can deliver numerous cells selectively to peri-infarct regions. Attention should be paid to possible complications of trepanation and cerebral puncture, such as epilepsy and hemorrhage due to cerebral injuries. In 2005, Kondziolka et al. reported a phase 2 trial with LBS-Neurons (human teratocarcinoma cell line origin, Layton BioScience, Inc.) [18]. They adopted the intraparenchymal cell transplantation technique for 14 patients with stroke. Serial evaluations demonstrated that one patient had a single seizure and one had an asymptomatic chronic subdural hematoma. In a recent report, Steinberg et al. described a phase 1/2A study, with SB623 cells (SanBio Inc., CA, USA) [19]. Eighteen patients with ischemic stroke underwent stereotactic transplantation in the chronic phase. In this trial, one patient had a single seizure and one had asymptomatic chronic subdural fluid collection.

In our protocol, all subjects will be taking fosphenytoin sodium hydrate to prevent epileptic seizures in the perioperative period. Moreover, we use a round head stereotactic cannula to prevent hemorrhagic events due to the procedure, while a thin and pointed cannula was used in the two previously mentioned trials.

The sample size of the trial was based on the traditional 3 + 3 dose escalation design. Indeed, it may be difficult to reach statistically significant differences with small number (6 to 10) of patients, but we think that such a small population can verify the safety. For examples, Savitz et al. reported the safety concerns of clinical trials about the stereotactic transplantation with LGE cells (Genvec Inc.) in only 5 stroke patients [20]. Because 2 patients had the adverse effects (the temporary worsening of motor deficits 3 weeks after transplantation and the seizures 1 week after transplantation), the trial was terminated by the FDA.

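### The sample size is attributed to a traditional 3+3 escalation design, but the allocation rule and the 6–10 range as written do not match one

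*Protocol article*

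**What the plan says.** In the protocol article, the section on sample size and statistical analysis first gives a pilot-study reason for the cohort size: "each group is composed of three subjects to examine the safety of HUNS001–01 administration". It then names the design: "The sample size of the trial was based on the traditional 3 + 3 dose escalation design". The Discussion section on safety measures for intraparenchymal injection repeats that claim.

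The rule that follows in the sample size section has these parts:

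- **Low dose:** "The first three subjects are included in the low-dose group".
- **High dose:** "the following three patients are included in the high-dose group".
- **Departure from three and three:** a change to the lower dose, where that is possible, on one stated ground: "if the cultured BMSCs are inadequate for the high-dose group on 74 days after the onset of stroke, a subject could be moved to the" (meaning the lower of the two doses).
- **Total and end of enrolment:** "In that case, the number of subjects will exceed six, and the last subject is the third subject in the high-dose group".
- **Cap:** 10 subjects, if a third high-dose subject has not been reached by then.

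The Abstract gives the enrolment estimate as 6–10, and the Discussion uses the same range. The primary end point is the frequency of adverse events over one year.

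**The concern.** In a 3+3 design the toxicity seen in one cohort decides what happens next: go up, add three more at the same dose, or stop. That dependence is what gives the design its safety property and determines its possible sizes. The article claims the label, but the only contingency it writes down is a manufacturing one.

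This matters for what the trial can later say. HUNS001–01 is described as first in human for this indication, it is injected into the brain, and safety is the primary aim. A reader who takes the 3+3 label at face value will conclude that treating anyone at the high dose means the low dose passed a toxicity test. The rule as written does not support that conclusion.

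**Working it through.** **Inputs from the article.** Two dose groups, three subjects each. First three low, next three high. Above six only after a cell-yield move. Enrolment ends at the third high-dose subject or at 10. Stated range 6–10.

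**Inputs assumed.** The article gives neither a 3+3 decision rule nor a toxicity rate. The textbook rule is assumed: 0 of 3 with toxicity, escalate; 1 of 3, add three and escalate if the total is 1 of 6; otherwise stop. True low-dose toxicity rates p of 10 to 50% are tried.

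**Step 1: reproduce the stated size.** 2 groups × 3 = 6. This matches the lower end of the range. It is also the total of a 3+3 in which no toxicity occurs and the top dose is not expanded.

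**Step 2: can the range 6–10 come from a two-level 3+3?** Each dose takes three or six subjects, and the trial can stop at the low dose. The possible totals are therefore 3 (stop after the first cohort), 6, 9 and 12 (6 + 6).

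- The floor of 6 leaves out stopping at 3.
- The cap of 10 is not a possible total and does not leave room for 6 + 6.
- Totals of 7, 8 and 10 cannot occur at all.

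Under the written rule, if each extra subject is a cell-yield move, ending with the third high-dose subject at 10 means 7 low + 3 high. A 3+3 never puts more than six at one dose. The extension thus enlarges the low-dose group for manufacturing reasons, not because of toxicity.

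**Step 3: how often would a 3+3 reach 12?** Exact enumeration was run over six pairs of low- and high-dose toxicity rates between 10% and 50%:

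| Textbook variant | Probability of needing 12 |
|---|---|
| No de-escalation | 0.04–0.09 |
| Low dose filled to six if the high dose is toxic | 0.09–0.29 |
| Top dose also filled to six | 0.19–0.35 |

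Twelve is the longest path, not the typical size.

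**Step 4: chance of moving to the high dose.** Under the assumed rule,

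P(escalate) = (1−p)³ + 3p(1−p)² × (1−p)³.

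For example, at p = 0.3: 0.343 + 0.441 × 0.343 = 0.343 + 0.151 = 0.494.

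| True low-dose toxicity rate | Textbook 3+3 | Rule as written, if no toxicity rule exists elsewhere |
|---|---|---|
| 10% | 0.906 | 1.0 |
| 20% | 0.709 | 1.0 |
| 30% | 0.494 | 1.0 |
| 40% | 0.309 | 1.0 |
| 50% | 0.172 | 1.0 |

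The last column sets cell yield aside.

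**Step 5: does an unseen rule repair the text?** No. If toxicity could expand a cohort, there would be a second route above six, and the article ties totals above six to cell yield. If toxicity could stop escalation, the statement that the next three subjects get the high dose would be conditional, and it is written without a condition.

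**The case against.** The strongest reply is that the article condenses a fuller protocol. Naming a traditional 3+3 conventionally brings the escalate, expand or stop rule with it, and toxicity definitions, evaluation windows and stopping rules are commonly left to the full document. On this reading, three low then three high is simply the no-toxicity path, and that path does give six.

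Much of this stands, and it limits the point. A reader might infer that the trial has no toxicity gate, that later subjects are unprotected, or that the high dose would be opened even after toxicity in all three low-dose subjects. The article does not support those as statements about the trial. It states no such rule, but the full protocol is not shown and may hold one. The 1.0 comparator is conditional for the same reason.

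Three other strong readings also fail:

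- **That 3+3 is the whole justification of the size.** The sample size section also appeals to the pilot nature of the study. The Discussion adds a five-patient precedent: "Because 2 patients had the adverse effects", that trial was terminated.
- **That this precedent contradicts the allocation.** It is cited to argue that a small sample can reveal safety problems. It says nothing about what this trial would do after such events.
- **That a 3+3 here would need 12 subjects.** That is only the maximum.

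The article also plans no formal maximum tolerated dose and presents its data descriptively, so a 3+3-based tolerability claim is a risk of interpretation, not a planned analysis.

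The objection does not remove the mismatch. The article does more than stay silent: it states who gets which dose, the reason for exceeding six, and when enrolment ends. No other section supplies a toxicity gate. The investigator-judgment criterion at second screening concerns an individual subject's suitability, and the monitoring section concerns data.

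**Conclusion.** The point holds as an inconsistency between the design named and the design written. The 6–10 range and its cell-yield trigger do not follow from a two-level 3+3, and enrolment-order allocation with no stated toxicity condition is not a 3+3 escalation. Confidence in this mismatch is high, because it rests on stated text.

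The size of the consequence is conditional. If no toxicity rule exists in the full protocol, the design differs from the one claimed by the margins in the escalation table, for example 1.0 against 0.49 at a 30% low-dose toxicity rate. If a rule does exist, the error lies in the article's account of allocation and size. The probabilities rest on the assumed textbook rule and the assumed rates.

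**What to change.** Reconcile the sample size section with the Discussion section on safety measures, and align the enrolment estimate in the Abstract.

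- **If no toxicity-driven rule exists:** remove the 3+3 justification in both places. Describe two sequential cohorts of three with cell-yield replacement up to 10 subjects, and draw no tolerability conclusion that relies on a 3+3.
- **If such a rule exists:** state it as the sponsor has defined it. Make the allocation and the reasons for exceeding six conditional on it, and restate the size range so that it fits the rule plus any cell-yield moves.

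The content of the clinical rule is for the sponsor, and this review proposes none. The first course is a wording amendment. The second adds a statement of the rule and a revised size range. In the first case the price is a less favourable stated justification for the sample size.

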### Characteristics of HUNS001–01

HUNS001–01 consists of plastic-adherent fibroblast-like cells. The phenotype of these cells is positivity for CD44, CD90, CD105, CD106, CD146, and CD 166, and negativity for CD19, CD34, and CD45. The expression of markers are consistent with the mesenchymal stromal cell phenotype according to the position statement of the International Society for Cellular Therapy (ISCT) [15].

### Preparation of HUNS001–01

The cell source for HUNS001–01 is obtained by extracting approximately 50 mL of bone marrow from each subject. The bone marrow is brought to the CPC at Hokkaido University Hospital, and the following processes are performed in a closed operation system (CPWS System Cell Processing Work Station, Panasonic Healthcare Co., Tokyo, Japan). BMMNCs are isolated via density-gradient centrifugation with Ficoll-Hypaque® (Pharmacia, Uppsala, Sweden), and 1 × 10^7^ cells are plated in a 175 cm^2^ uncoated flask (Easy Flask 159,910; Nunc) with 25 mL of αMEM with 10% hPL derived from healthy volunteers and 40 μg/mL of gentamicin sulfate. About the preparation of hPL, our previous report about safety and efficiency of hPL should be referred to [4]. After 24 h, nonadherent cells are removed by changing the medium. The culture medium is replaced 2 times a week. The BMSCs are passed two or three times for the subsequent procedure. In order to label the cells for MRI tracking, 1 μL/mL ferucarbotran (27.9 μg Fe/mL, Resovist®, Fuji lm RI Pharma Co., Ltd., Tokyo, Japan), a SPIO agent, is added into the culture medium and incubated with the BMSCs for 24 h before the cell injection procedure. The SPIO-labeled BMSCs in flasks are lifted using TrypLe Select® (a recombinant trypsin substitute, Gibco) and centrifuged. The supernatant is decanted and the cells are gently resuspended in Artcereb® (irrigation and perfusion solution used for cerebrospinal surgery; Otsuka Pharmaceutical Factory, Inc., Naruto, Japan) to a concentration of 5 × 10^7^ cells/mL.

### Intervention

On the day when HUNS001–01 is manufactured, the cell product will be administered to the subject. A dose of 2 × 10^7^ cells (400 μL) will be administered in the low-dose group and a dose of 5 × 10^7^ cells (1000 μL) will be administered in the high-dose group. HUNS001–01 is implanted using MRI stereotactic technique to define the target sites in the normal white matter around the lesion. The number of target sites is one or two in the low-dose group, and two or three in the high-dose group. The subject has a one or two burr-hole craniotomy under local anesthesia and sedation. Using 2.1-mm outer diameter stereotactic cannula, 200 to 500 μL of the product is injected over a period of 5 min at each site. The cannula is removed after 5 min after finishing the injection at each site. In the perioperative period, all subjects take fosphenytoin sodium hydrate to prevent epileptic seizure due to the procedure.

### End point of the study

#### Primary end point

Safety of HUNS001–01 administration for 1 year after the intervention: frequency of Adverse Event (AE)

#### Secondary end points

Safety of HUNS001–01 administration for 30 days after the intervention: frequency of Adverse Event (AE)Safety of bone marrow aspiration: frequency of Adverse Event (AE)Frequency of the defects of HUNS001–01 at manufacturingImprovement of stroke symptoms for 1 year after the intervention using the following assessment scales:ational Institute of Health Stroke Scale (NIHSS)modified Rankin Scale (mRS)Functional Independence Measure (FIM)Barthel IndexFugl-Meyer Assessment
Improvement in lesion volume assessed by MRI analysis for 1 year after the interventionAssessment of cell distribution using MRIAssessment of possible functional shift for 1 year after the intervention using FDG-PET and IMZ-SPECT

### Follow-up of study

The schedule of follow-up of study is as follows (Table 1):Vital signs, serological, and biochemical tests: Days 0, 1, 3, 7, 14, 30, 90, 180, 360Urinalysis: Days 30, 90, 180, 360Urine hCG-β (if needed): Days 90, 180, 36012-lead electrocardiogram and chest X-ray examination: Days 1, 7, 30, 90, 360Neurological examination (NIHSS, mRS, FIM, Barthel Index, Fugl-Meyer Assessment): Days 1, 3, 7, 14, 30, 90, 180, 360MRI: Days 0, 3, 7, 14, 30, 90, 180, 360FDG-PET and IMZ-SPECT: Days 30, 90, 360

**Table 1 Tab1:** The schedule of follow-up of study

	Screening			Follow up									
	1st screening	BM hervest	2nd screening	Pre-administration	Post-administration								
	Onset to14 days		Day −7 (±1)	Day 0		Day 1	Day 3	Day 7	Day 14	Day 30 (±3)	Day 90 (±30)	Day 180 (±30)	Day 360 (±30)
Informed consent	X												
Medical history	X												
Vital signs	X	X	X	X	X	X	X	X	X	X	X	X	X
Body weight and height	X												
Serological tests	X		X		X	X	X	X	X	X	X	X	X
Biochemical tests	X		X		X	X	X	X	X	X	X	X	X
Urinalysis	X		X							X	X	X	X
Urine hCG-β (If needed)	X									X	X	X	X
Infectious disease inspection	X												
12-lead electrocardiogram	X		X			X		X		X	X		X
Chest X-ray examination	X		X			X		X		X	X		X
Neurological examination	X		X			X		X		X	X	X	X
MRI	X		X	X	X		X	X	X	X	X	X	X
FDG-PET and IMZ-SPECT			X							X	X		X
Bone marrow harvest		X											
Cell product administration				X									
Concomitant medication	X	X	X	X	X	X	X	X	X	X	X	X	X
Adverse events	X	X	X	X	X	X	X	X	X	X	X	X	X

### Data collection and monitoring

All data are collected by appointed staff members, who are approved by the Clinical Research and Medical Innovation Center, Hokkaido University Hospital. They are monitored by the Standard Operating Procedures (SOPs) of Good Clinical Practice (GCP) and the ICH guidelines.

### Ethics and dissemination

This trial is conducted following the GCP guidelines and the principles of the Declaration of Helsinki. The data obtained in this study will be disseminated in peer-reviewed journals and presented at international scientific meetings.

## Discussion

### Subject screening

Current therapeutic strategies for ischemic stroke typically aim to improve blood flow in ischemic areas or to relieve neuronal damage through neuroprotective effects before the ischemic disorder is established. However, in cell therapy, some strategies aim to resolve neurological disorders resulting from an established cerebral infarction. Autologous cell products, in particular, require time for tissue collection and manufacturing. If changes in a subject’s condition are anticipated during the manufacturing period, appropriate screening at the start of the administration, as well as at the enrollment should be established.

In our trial, NIHSS score is assessed in the first screening on day 14 after the onset. The NIHSS is used for systematic assessment of potential symptoms and signs of stroke, and is designed primarily to assess symptoms and signs in the acute phase and to determine the severity of the disease. On the other hand, mRS, which is one of the disability measures, has been widely used as an efficacy endpoint in clinical trials all over the world. In our trial, mRS is examined in the second screening, 7 days before the administration. H, the NIHSS score on admission is inadequate for the first screening. Due to the weak correlation with the mRS score in chronic phase, possible dropouts are expected at the second screening. In fact, Kimura et al. reported that approximately half of the subjects with NIHSS scores of 7–10 at admission would have an mRS score of 0–2 at discharge [16]. We adopted the NIHSS on day 14 after the onset, but not on admission, as the first screening, because it has a stronger correlation with the mRS score and other outcome scales in the chronic phase [17].

In the trial, we enrolled patients who met the inclusion criteria of a total score of NIHSS ≥6, and a “Motor Arm” and “Motor Leg” score of NIHSS ≥6 at the first screening, since the improvement of injured motor function is an anticipated result of the administration of HUNS001–01.

### Safety measures for intraparenchymal injection

Intraparenchymal injection is a technique to administer cells directly into the cerebral parenchyma. This technique can deliver numerous cells selectively to peri-infarct regions. Attention should be paid to possible complications of trepanation and cerebral puncture, such as epilepsy and hemorrhage due to cerebral injuries. In 2005, Kondziolka et al. reported a phase 2 trial with LBS-Neurons (human teratocarcinoma cell line origin, Layton BioScience, Inc.) [18]. They adopted the intraparenchymal cell transplantation technique for 14 patients with stroke. Serial evaluations demonstrated that one patient had a single seizure and one had an asymptomatic chronic subdural hematoma. In a recent report, Steinberg et al. described a phase 1/2A study, with SB623 cells (SanBio Inc., CA, USA) [19]. Eighteen patients with ischemic stroke underwent stereotactic transplantation in the chronic phase. In this trial, one patient had a single seizure and one had asymptomatic chronic subdural fluid collection.

In our protocol, all subjects will be taking fosphenytoin sodium hydrate to prevent epileptic seizures in the perioperative period. Moreover, we use a round head stereotactic cannula to prevent hemorrhagic events due to the procedure, while a thin and pointed cannula was used in the two previously mentioned trials.

The sample size of the trial was based on the traditional 3 + 3 dose escalation design. Indeed, it may be difficult to reach statistically significant differences with small number (6 to 10) of patients, but we think that such a small population can verify the safety. For examples, Savitz et al. reported the safety concerns of clinical trials about the stereotactic transplantation with LGE cells (Genvec Inc.) in only 5 stroke patients [20]. Because 2 patients had the adverse effects (the temporary worsening of motor deficits 3 weeks after transplantation and the seizures 1 week after transplantation), the trial was terminated by the FDA.

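### Six to ten patients can reveal gross harm but cannot verify safety: with no occurrence of a given complication, risks up to 39% (n=6), 26% (n=10) or 63% (three high-dose patients) remain compatible

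*Protocol article*

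**What the plan says.** The sample size section of the protocol article states that "each group is composed of three subjects to examine the safety" and that "The sample size of the trial was based on the traditional 3 + 3 dose escalation design". Three patients receive the low dose and the next three the high dose. If too few cells grow for the high dose, a patient may move to the low-dose group, so the total can exceed six. On the upper end: "The total number of subjects is limited to 10 if a third subject in the high-dose group is not accomplished".

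The primary end point is the frequency of adverse events over one year. The planned summary is descriptive: "Categorical data will be presented as absolute frequencies or relative percentages".

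The Discussion section on safety measures for intraparenchymal injection returns to the sample size. It concedes that "it may be difficult to reach statistically significant differences with small number (6 to 10) of patients", and then continues that "we think that such a small population can verify the safety". The example offered is a trial of LGE cells in 5 stroke patients, stopped after 2 had adverse effects. The same section cites two larger intraparenchymal trials, of 14 and 18 patients. Each had one patient with a seizure and one with an asymptomatic subdural event.

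**The concern.** The example runs in one direction only. Two affected patients out of five show that a handful of patients can be enough to reveal a hazard of the order of 40%. They say nothing about what may be concluded when few or no patients are affected, and that is the situation in which someone would claim that safety had been verified.

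The concession just before the claim does not cover this. It concerns significant differences, whereas the question for a safety trial without a control group is how tightly a risk can be bounded. The sample size section is more careful, since it speaks only of examining safety.

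Safety is the primary aim, and this is a first-in-human trial of the product by intracerebral injection. A clean result read in the light of this sentence would be taken as verified safety, although the data could not exclude risks well above those in the trials the article itself cites.

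**Working it through.** **The plan's own figure.** 2 dose groups × 3 patients = 6, which matches the article. The 10 is a fixed cap and is not derived. The article attaches no event rate to be excluded and no precision to the claim, so nothing further can be reproduced.

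**Inputs.** From the article: n = 3 per dose, 6 to 10 in total; seizures in 1 of 14 and 1 of 18 patients; subdural events in 1 of 14 and 1 of 18; adverse effects in 2 of 5. Assumed: a 95% confidence level, independent patients and, for the pooled rows, the same risk at both doses.

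**Step 1: what a clean result excludes.** For a specified complication with 0 occurrences in n patients, the exact upper limit is 1 − 0.05^(1/n) one-sided and 1 − 0.025^(1/n) for the two-sided interval.

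| n | One-sided 95% | Two-sided 95% |
|---|---|---|
| 3 (high-dose group) | 63.2% | 70.8% |
| 6 | 39.3% | 45.9% |
| 10 | 25.9% | 30.8% |

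Recruiting beyond six does not help the high dose. The extra patients arise because high-dose candidates are moved to the low dose, and recruitment ends with the third high-dose patient. If the cap of 10 is reached first, there are fewer than three high-dose patients and the limit is wider.

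**Step 2: cited rates.**
- Seizure, two larger trials: (1 + 1)/(14 + 18) = 2/32 = 6.25%, exact 95% CI 0.8% to 20.8%.
- Seizure or subdural event, same trials: (2 + 2)/32 = 4/32 = 12.5%, exact 95% CI 3.5% to 29.0%.
- LGE-cell trial: 2/5 = 40%.

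**Step 3: probability of seeing no event, (1 − p)^n.**

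| Rate p | n = 3 | n = 6 | n = 10 |
|---|---|---|---|
| 6.25% | 82.4% | 67.9% | 52.4% |
| 12.5% | 67.0% | 44.9% | 26.3% |
| 40% | 21.6% | 4.7% | 0.6% |

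For example, 0.9375^6 = 0.679 and 0.875^10 = 0.263.

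**Step 4: limits against cited rates.** The one-sided limit for 0/6 is 39.3/6.25 = 6.3 times the seizure rate and 39.3/12.5 = 3.1 times the combined rate. For 0/10 the ratios are 25.9/6.25 = 4.1 and 25.9/12.5 = 2.1.

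**The case against.** The strongest reply is that this is a hedged opinion in a Discussion. It sets no end point, decision rule or analysis, three per dose is customary in a 3 + 3 design, and the sample size section states the aim modestly. All of that is true, and it places the fault in the inference and not in the number of patients. It does not make the claim correct, and the claim is part of the article's justification of its sample size.

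Stronger readings are tempting, and the documents do not support them:

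- A reader might infer that the trial would probably miss complications at the cited rates. That holds only for a single complication at about 6%. A miss is more likely than not only if the true rate is below 1 − 0.5^(1/6) = 10.9% (n=6) or 1 − 0.5^(1/10) = 6.7% (n=10). At the combined 12.5%, at least one event is seen with probability 55% or 74%; at 40%, with 95% or 99%.
- A reader might infer that significance is impossible, so that the article's concession is too mild. This is so for 3 versus 3, where the smallest two-sided Fisher p is 2/20 = 0.10. The conceding sentence covers 6 to 10 patients, however, and with 4 versus 3 the smallest p is 1/35 = 0.029. Its wording is fair.
- A reader might picture a primary result of 0%. All-cause adverse events over a year after burr-hole surgery are unlikely to be zero. The zero-event limits apply to specified complications.
- Intervals, counting by patient or by event, and a breakdown of serious events commonly stand in a statistical analysis plan, which is not at hand. Their absence from the article is not a fault.

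**Conclusion.** The claim is wrong as written. The design can detect gross harm, of the order seen in the 2-in-5 example, with high probability. It cannot verify safety. A clean result for a given complication leaves risks up to 39% (n=6), 26% (n=10) or 63% (high dose alone) compatible with the data, one-sided.

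These limits depend on the assumed 95% level and on independence; the pooled ones also treat the two doses as having one risk. The probabilities of seeing no event are less firm, because the cited rates rest on two and four events. The article hopes that seizure prophylaxis and a round-headed cannula will lower the rates; if they do, a clean result becomes more likely and tells less about safety. The point is one of stated inference. It is no argument for a larger trial.

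**What to change.** In the Discussion, replace the claim that the population is large enough to verify safety with a statement that the trial can detect only gross harm. For example: *With 6 (10) patients and no occurrence of a given complication, risks above 39% (26%) are excluded with one-sided 95% confidence; with three high-dose patients, only risks above 63%.* The sentence on significant differences can stay.

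In the results, report the procedural complications that the article names (seizure, intracranial haemorrhage or fluid collection, motor worsening) as patients affected, n/N, with exact confidence limits, by dose received and overall. If an analysis plan already provides this, only the Discussion sentence needs changing.

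The cost is a sentence and a few table columns. No extra patients are needed and nothing in treatment or procedures changes. The price is a less favourable statement of what the trial can show.
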